#### Sample size requirements

Given that this study is a mixed-methods design, the sample size was based on the quantitative analyses as these have larger sample size requirements. Sample size estimation was based on detecting an effect of 0.50 between groups on any of the three aspects of outcome (knowledge, utilization, and integration into clinical reasoning). Assuming Type I error = 0.05 (2-tailed); Type II error = 0.80; Effect size = 0.50, the sample size required per group = 64. The sample size required for two-comparison groups = 128 and accounting for a 10% dropout = 128/0.9 = 142. We anticipate low dropouts given the priority of continuing education by both professions. We will round our sample size up to 144 to provide a number equally divided between three sites, requiring 48 per site. Based on the need to allocate participants in blocks to interventions and to balance professions and clinical areas evenly, we expect to accommodate 24 participants per intervention group, per site. These will consist of three tutorial groups of eight therapists/groups. Given the distribution of practice patterns in rehabilitation, we expect two groups on orthopedics and one group on pediatric practice at each location. Groups will be formed according to practice settings to insure that the stakeholders can develop "problems" that simulate their own clinical settings/populations.

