#### Stakeholder-Hosted Interactive Problem-based Seminars (SHIPS)

The SHIPS will consist of a 2 1/2-day interactive PBL sessions with 10 hours of contact/tutorial time and 15–20 hours of facilitated independent group work that will focus on application of learned concepts. Consistent with a problem-based philosophy, small groups of clinicians will participate in interactive sessions facilitated by a faculty tutor. The faculty tutor will be a developer of outcome measures, an expert facilitator in PBL, and one of the study investigators. The SHIPS' knowledge transfer strategy is based on evidence establishing the importance of using opinion leaders with scientific and professional credibility [32], and will be operationalized using our experience in PBL as a method of providing contextualized learning. Six "problems" will be generated by faculty through a consultative process with the participants prior to the sessions. Problems will be generated to reflect the established curriculum, with a problem that represents the practice characteristics and issues expressed by participants. Participants will conduct this process four weeks prior to the SHIPS intervention and will receive the curriculum, course objectives, and a recommended reading list one week prior to attendance at the SHIPS.

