## Analyses

### Quantitative analyses

All data will be double-entered in SPSS 14.0. Descriptive analyses will be conducted, including checking for outliers, normality testing, and univariate correlations. The first primary analysis (Objective 1) will be a two-way repeated measures analysis of variance to determine primary unadjusted differences in absolute scores over time, and between groups for each of the three primary outcome measures: knowledge, utilization, and chart-stimulated recall scores. An analysis of covariance will be used to compare these same effects adjusting for baseline knowledge score, Readiness to Change, years of practice, and educational preference. These analyses across the e-PBL and SHIPS groups will determine the relative effectiveness of these two alternative knowledge transfer choices. Effect sizes and their 95% confidence intervals will be calculated to determine whether there are differential impacts on change in knowledge, utilization, and integration of knowledge between the two different KT approaches. For the secondary research question (Objective 2.3) on the relative importance of KT predictors, a multiple linear regression [79,80] will be used to develop models of how years of practice, educational background, caseload characteristics, educational preferences, or Readiness to Change predict changes in knowledge, utilization, or integration following knowledge transfer interventions, with KT method as a covariate.

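### Both arms are taught in tutorial groups of eight, but the sample size and the named analyses treat therapists as independent; any correlation within groups makes the stated power optimistic and the standard errors too small

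*Protocol article*

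**What the plan says.** All references are to the protocol article.

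- **Sample size requirements.** The calculation uses a two-sided 5% level and an effect of 0.50 on any of the three outcomes: "Effect size = 0.50, the sample size required per group = 64". The only inflation is for 10% dropout (128/0.9 = 142), rounded up to 144, or 48 per site. The same paragraph then places the 24 participants per arm per site in groups: "These will consist of three tutorial groups of eight therapists/groups". It expects two orthopedic groups and one pediatric group at each location.
- **SHIPS.** The teaching unit is the group: "small groups of clinicians will participate in interactive sessions facilitated by a faculty tutor".
- **e-PBL.** Discussion questions are worked through in online chat among participants, led by faculty tutors.
- **Quantitative analyses.** Objective 1 is addressed by a "two-way repeated measures analysis of variance to determine primary unadjusted differences in absolute scores over time" and between groups. An ANCOVA follows on four person-level covariates (baseline knowledge, Readiness to Change, years of practice, educational preference). A multiple linear regression addresses predictors. No tutorial-group, tutor or site term appears in any of them.
- **Group assignment procedure.** Allocation takes place within orthopedic and pediatric groups at each site. Participants are paired on profession, practice area, pre-test score and years of practice.

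**The concern.** The interventions work through small-group interaction, and the Background section itself names tutorial discussion as an active component of problem-based learning. Therapists who share a tutor and a discussion may therefore end up more alike than therapists in different groups of the same arm. This correlation arises after allocation and differs between the arms, so it adds variance to the arm difference that an analysis of individuals does not see.

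The comparison of SHIPS with e-PBL is Objective 1. Differences between a few groups or tutors could be read as an effect of delivery mode, with confidence intervals that are too narrow. An analysis that did respect the groups would have less power than the paragraph promises. The repeated-measures structure handles correlation within a therapist over time; it does nothing for correlation between therapists in one group.

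**Working it through.** **Inputs from the article:** two-sided alpha 0.05; effect 0.50 SD; 64 per arm; 10% dropout; 144 enrolled; 24 per arm per site in three groups of eight. The article labels 0.80 as Type II error. Its figures fit 80% power (a literal Type II error of 0.80 would need only about 11 per arm), so I read it as power.

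**Reproducing the plan's figure.** The noncentral-t two-sample calculation for independent observations gives power 0.801 at 64 per arm, and 128/0.9 = 142.2. The stated 64, 128 and 142 therefore reproduce, but only for independent people.

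**Clusters.** 3 groups × 3 sites = 9 per arm; 9 × 2 = 18 in all. After 10% dropout, m = 8 × 0.9 = 7.2 per group and n = 9 × 7.2 = 64.8 per arm.

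**Formulas.**
- Design effect DE = 1 + (m − 1) × ICC.
- Effective n per arm = 64.8/DE.
- SE of the arm difference, in SD units = √(2 × DE/64.8).
- Power from a noncentral t with noncentrality 0.50/SE, on 18 − 2 = 16 df (analysis at group level) or on individual df (about 128).
- Type I error of the analysis that ignores groups ≈ 2 × (1 − Φ(1.96/√DE)).

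**Worked case, ICC 0.05.** DE = 1 + 6.2 × 0.05 = 1.31. SE = √(2 × 1.31/64.8) = 0.201. Noncentrality = 0.50/0.201 = 2.49. Power is 0.65 on 16 df and 0.69 on individual df. Naive type I error = 2 × (1 − Φ(1.96/1.145)) = 8.7%.

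The article gives no ICC, so the values below are assumptions. No allowance is made for matching or baseline adjustment.

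| ICC | DE | Effective n per arm | Power, 16 df | Power, individual df | Naive type I error |
|---|---|---|---|---|---|
| 0 | 1.00 | 64.8 | 0.76 | 0.81 | 5.0% |
| 0.01 | 1.06 | 61.0 | 0.74 | 0.78 | 5.7% |
| 0.02 | 1.12 | 57.7 | 0.71 | 0.76 | 6.4% |
| 0.05 | 1.31 | 49.5 | 0.65 | 0.69 | 8.7% |
| 0.10 | 1.62 | 40.0 | 0.56 | 0.60 | 12.4% |

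On 16 df, the effect detectable with 80% power is 0.60 at ICC 0.05 and 0.67 at ICC 0.10. Correct confidence intervals are wider than the naive ones by √DE, about 1.14 and 1.27. Fixed effects for site (2 df) and practice area (1 df) would leave 13 df, with power 0.63 at ICC 0.05.

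**If all 144 are retained** (m = 8, 72 per arm), power at ICC 0.02 is 0.75 on 16 df and 0.80 on individual df. At ICC 0.05 it is 0.68 and 0.73.

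**The case against.** Several points on the other side have force.

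- **Practice setting.** A reader might infer that forming groups by practice setting is what inflates the error. It is not. The same orthopedic and pediatric strata are planned in both arms at every site, so variation shared by the arms within a stratum cancels from the difference. Only correlation created after allocation counts.
- **Matching.** A naive test that ignores the pairing is conservative, which works against the clustering. In a simulation with assumed variance shares of 0.05 for stratum and 0.20 for pair, the naive type I error was about 4% at group ICC 0.02 and about 6 to 6.5% at 0.05. A reader might infer that the false-positive rate must exceed 5%; the documents do not establish that. The percentages in the table are no-matching figures.
- **Baseline adjustment.** The ANCOVA adjusts for baseline knowledge. With an assumed baseline correlation of 0.5 the SE shrinks by √(1 − 0.25) = 0.87, and power on 16 df becomes 0.83 at ICC 0.02 and 0.77 at 0.05. The gain is clearest for the knowledge outcome.
- **A condensed article.** Random terms and degrees-of-freedom methods are often left to an analysis plan that is not shown. That would answer silence. Here, however, the article names the test families and the covariates, and it computes the sample size for individuals in the paragraph that describes the groups.

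These points limit the size of the problem. None of them removes correlation from a shared tutor and shared discussion. If one tutor leads several groups, which the article does not settle, there are fewer than 18 independent units.

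**Conclusion.** The concern holds in conditional form. The design has 18 tutor-led groups, while the sample size and the named models assume independent individuals. If tutorial-group correlation is present, the stated 80% power is optimistic and the standard error of the arm difference tends to be too small. For an assumed ICC of 0.02 to 0.10, with the planned dropout and no credit for matching or baseline adjustment, power is 0.71 to 0.56 on 16 df (0.76 to 0.60 on individual df), and the naive type I error is at most about 6% to 12%. At ICC 0.01 the effect is small.

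Two stronger readings are not supported. A reader might infer that the effective replication is 18 groups and not 144 people. That would require an ICC of 1; at ICC 0.05 to 0.10 the effective sample is about 49 to 40 per arm. A reader might also infer that 80% power holds exactly when there is no group correlation. On 16 df and after dropout it is already 0.76 at ICC 0, whereas with all 144 retained it is still about 0.80 on individual df at ICC 0.02. The answer depends on degrees of freedom and retention as well as on the ICC.

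**What to change.** Keep n = 144.

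1. Record each therapist's tutorial group in both arms. Fit the between-arm comparisons as mixed models (generalized for the utilization counts) with a random intercept for tutorial group, fixed effects for site and practice area, the planned baseline covariates, and small-sample degrees of freedom (Satterthwaite or Kenward-Roger).
2. Restate the sample-size paragraph: 64 per group gives 80% power only for an analysis of independent individuals. Then give the power or detectable effect over an assumed ICC range of about 0.01 to 0.10, on the degrees of freedom of the mixed model.

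The cost is slightly more analysis work and a less favourable stated power. No extra participants are needed, and group membership is known from the delivery of the courses. The change does not restore the lost power; it makes the inference honest about it.

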#### Group assignment procedure

A randomized design is usually the most rigorous, allowing for control of known and unknown confounders. In this case, it is not the most appropriate design strategy and we have selected a quasi-experimental approach. Research design methodologists have indicated that attaining an equal distribution of confounders in small samples via randomization, such as that required for the present study, is unreliable. Therefore we will use a non-randomized allocation procedure called minimization, which places participants in intervention groups to minimize the differences across key predictors [69-71]. We have identified pre-test scores, years of practice, practice area (urban/rural), and practice type (PT/OT) as the key predictors. Minimization across key predictors will balance prognostic variables and result in more valid comparisons [71]. Subjects will be allocated using minimization within orthopedic and pediatric groups at each site. At each site the pool of subjects will be allocated minimizing difference by: creating pair groupings based on professional training (PT/OT), matching area practice and then most similar pre-test scores, and, finally, by minimizing years of practice. We then will conduct descriptive analyses of group similarities and test whether we can optimize groups' consistency by reallocation of assignment. When this process is complete, subjects at each site will be informed of their assignment.

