### Study measures

#### Baseline measurement of eligibility, status, and potential KT predictors

Participants will be pre-screened to ensure inclusion criteria. Eligible participants will then complete a baseline knowledge pre-test (to avoid ceiling effects/lack of responsiveness). Participants also will complete a baseline information questionnaire to collect demographic data, practice patterns, and educational background. Survey measures of knowledge and behavior will be administered. This data collection also will include a measurement of the therapist's intent to use outcome measures, their general level of research utilization, and their readiness to change. This scale evaluating Readiness to Change [40,41,73] was developed to reflect the core elements of the five stages of change, but was specifically applied to changing clinical practice. Although all participants will have agreed to allocation during informed consent, they will be asked their preference with respect to e-PBL and SHIPS so that post-hoc analyses can determine the importance of educational preference as a mediator of response.

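### Allocation is non-random with an open reallocation step, although random assignment within the planned pairs, under a preset balance limit, would meet the only objection raised to randomising

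*Protocol article*

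**What the plan says.** The section on the group assignment procedure grants that randomisation is usually the most rigorous design and controls known and unknown confounders. It then says that here "it is not the most appropriate design strategy and we have selected a quasi-experimental approach". The reason given is that "attaining an equal distribution of confounders in small samples via randomization, such as that required for the present study, is unreliable". The consequence follows: "Therefore we will use a non-randomized allocation procedure called minimization".

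The steps are these:
- Allocation is done within orthopedic and pediatric groups at each site, on the assembled pool: "At each site the pool of subjects will be allocated minimizing difference by".
- Pairs come first: "creating pair groupings based on professional training (PT/OT), matching area practice and then most similar pre-test scores", with years of practice last.
- The groups are described and compared, and the team will "test whether we can optimize groups' consistency by reallocation of assignment".
- Participants hear the result only at the end: "When this process is complete, subjects at each site will be informed of their assignment".

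Elsewhere, the baseline measurement section says of participants that "they will be asked their preference with respect to e-PBL and SHIPS", for use in post-hoc analyses. The quantitative analysis section names an unadjusted repeated measures analysis of variance first. An analysis of covariance follows, on baseline knowledge, Readiness to Change, years of practice and educational preference.

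**The concern.** The article does not say how the two members of a pair are assigned to arms, what would trigger a reallocation, when reallocating stops, or who decides. The step that randomisation would protect is therefore open to judgement. The SHIPS section makes a study investigator the faculty tutor, so the study team delivers one of the arms being compared.

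At stake is Objective 1, the comparison of the two interventions. Balancing four named predictors says nothing about the rest. Employer support is neither a balancing factor nor a listed covariate. Baseline utilization is likewise in neither list, although utilization is one of the three primary outcomes. Non-random assignment also gives the tests and confidence intervals no randomisation basis. It cannot be repaired once the groups have been taught.

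**Working it through.** **1. The plan's own figures.** Inputs from the sample size section: two-sided alpha 0.05, effect 0.50 SD, and 0.80 read as power. The t-test calculation gives 63.8, so 64 per group and 128 in total, as stated. Then 128/0.9 = 142.2, and the plan rounds up to 144. That is 72 per arm and 24 per arm per site. Each arm at a site has two orthopedic groups and one pediatric group of eight, so 16 + 8 = 24 pairs per site and 3 × 24 = 72 pairs. Nothing here depends on how pair members are assigned.

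**2. Is the objection to randomisation sound?** For simple randomisation, in part. With 72 per arm the standard error of a standardised baseline difference is √(2/72) = 0.167. A difference above 0.25 SD is 0.25/0.167 = 1.5 standard errors, with probability 13% for any one predictor.

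**3. Does it also rule out randomising within pairs?** This was simulated: 144 people, three sites, 32 orthopedic and 16 pediatric per site, 1,000 replicates for each of three assumed mixes of PT/OT and urban/rural (50/80, 70/80 and 70/50 percent PT/urban). The article gives no mixes.

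| Scheme | Mean absolute pre-test difference (SD) | Any of four predictors beyond 0.25 SD |
|---|---|---|
| Simple 1:1 randomisation | about 0.13 | 41–45% |
| One coin flip per pair | about 0.10 | 18% |
| Within pairs, best of 100 random draws | about 0.02 | 0% |

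In the last scheme the 95th percentile of the absolute difference was at most about 0.06 SD on every predictor.

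Three features of the simulation matter.
- Pairs were formed on profession, area and pre-test score but not on years of practice, which the plan matches last. The 18% is therefore somewhat pessimistic for the plan's own pairs.
- Best of 100 draws stands in for a preset limit. It is not the only form of restriction.
- All three sites were drawn together, whereas the plan runs one site first. Drawing site by site is somewhat looser. However, with equal arms of 24 the overall difference is the average of the three site differences, so a limit met at each site is also met overall.

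**4. How much could allocator influence matter?** Illustration only. Assume an unmeasured factor correlated 0.3 with outcome and independent within pairs, with the more favourable member sent to one arm with probability p. The expected within-pair gap is 2/√π = 1.128 SD, so bias = (2p − 1) × 1.128 × 0.3. Dividing by 0.167 gives the shift in the test statistic.

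| p | Bias (SD) | Actual error at nominal 5% |
|---|---|---|
| 0.5 (random) | 0 | 5% |
| 0.6 | 0.2 × 0.338 = 0.07 | about 7% |
| 0.7 | 0.4 × 0.338 = 0.14 | about 13% |
| 1.0 | 1.0 × 0.338 = 0.34 | about 53% |

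The article gives no information on p or on the correlation.

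**The case against.** The design is openly called quasi-experimental and cites method papers that are not at hand, so nothing is concealed or mislabelled. The pool is formed before allocation, consent covers either arm, and participants learn their arm last. This limits self-selection and enrolment with foreknowledge. Those points stand, but they restrain the participant and not the allocator.

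A reader might infer more than the text supports, in four ways.
- **That assignment is deterministic and adjusted by hand, by staff who know each person's preference.** The article says only that it is non-random and that reallocation may follow a check of group similarity. It does not say who acts or what they see, and a fuller protocol may. It gives post-hoc analysis as the purpose of the preference question.
- **That selection bias is built in.** Only the opportunity for it can be read from the text.
- **That a bare coin flip per pair would give the same balance.** It keeps members of a pair alike but leaves arm means looser, as the 18% shows. The authors' small-sample worry partly survives that remedy, so the balance limit has to be part of the main fix.
- **That motivation and preferred mode go uncontrolled.** Preference is measured and is a covariate. Motivation is partly captured by intent and by Readiness to Change, and the latter is a covariate.

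Baseline utilization also needs care. Baseline behavior is surveyed, and utilization is analysed over time, so earlier levels are not ignored. Similarly, the abstract lists self-reported barriers at baseline, which may touch on employer support. Neither is balanced or named as a covariate.

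**Conclusion.** The point holds as a design weakness with an insufficient justification. The stated reason counts against simple randomisation, not against restricted randomisation within the pairs the plan already forms. The cost is an avoidable loss of protection against unknown confounders and an unregulated opening for allocator influence, in the primary comparison and across all 144 participants.

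That restricted randomisation can deliver the balance sought rests on the simulation, with its assumed mixes and a joint draw across sites. The bias figures of 0.07 to 0.34 SD, set against a target effect of 0.50, follow entirely from assumed inputs and are not estimates for this study. The change should be made before the first site allocates.

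**What to change.** Rewrite the allocation paragraph as follows.
1. Keep the pairing within site and orthopedic/pediatric group.
2. Fix in advance, for each site, a limit on the between-arm difference in pre-test score, years of practice, urban/rural practice and PT/OT. Check by simulation that many assignments satisfy it.
3. Draw by computer, at random, among the within-pair assignments that satisfy the limit. The person running the draw should not recruit, tutor or assess, and should not have the preference data.
4. Replace the open reallocation step with this rule.
5. Describe the trial as matched-pair (restricted) randomised, and reflect the pairs or strata in the analysis.

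The cost is a short script, a rewritten paragraph, a little more analysis work, and slightly looser arm balance than full optimisation would give. N stays 144, with 24 per arm per site. Tutorial group sizes and batch timing do not change.
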